#### Fifteen outcomes

We have 15 primary outcomes: 1) Alcohol Use Disorders Identification Test (AUDIT-C) score < 3 (i.e., problematic alcohol use); 2) no alcohol usage in last 24 h; 3) PEth Alcohol Test (excessive alcohol use in prior 3 weeks, at 24 months only); 4) no marijuana (dagga) usage in the last 10 days assessed via RDT; 5) no quaalude (mandrax) usage in the last 2–3 days assessed via RDT; 6) no methamphetamine (tik) usage in the last 1–2 days assessed via RDT; 7) HIV testing in the last 3 months; 8) employment (part/full-time); 9) income above 1200 ZAR/month; 10) no concurrent partnerships; 11) no sex without condoms; 12) no violent acts toward women; 13) no arrests by police; 14) engaged in a community activity; and 15) Center for Epidemiologic Studies of Depression (CES-D) score < 16 (i.e., caseness). Each primary outcome measure is a binary variable (not present or present).

#### Substance abuse

A combination of rapid diagnostic tests (RDT) and the AUDIT-C [9, 50, 51] assess substance abuse. The RDT includes the REDLINE Breathalyzer (determines alcohol use in the last 24 h), the PEth Alcohol Test (assesses excessive alcohol use in the last 3 weeks, at 24-month assessment only), and urine tests for marijuana, methamphetamine, and mandrax which document the alcohol or drugs as present (0) or not (1). The AUDIT-C is a brief, reliable and valid, three-item questionnaire of problematic alcohol use for which the time frame was adapted to shift from 12 months to 6 months. The three questions, each with a range of 1 to 4, cover the frequency of: 1) days of any alcohol consumption; 2) usual number of drinks daily; and 3) days on which > 6 drinks are consumed. The AUDIT-C demonstrates good sensitivity and specificity at a cut point of 3 or greater for identifying risky drinking (0) or not (1) and performs well in South Africa [9].

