#### Mental health

Mental health is evaluated by 20 items, each with a response range from 0 to 3, reflecting endorsement of symptoms of depression on the CES-D scale [47]. The scale has been found reliable (alpha > 0.85) in previous research [48]. Participants with a CES-D score greater than 16 are considered to have a depressed mood (0) and those < 16 are not (1).

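### The stated AUDIT-C item range (three items, each 1 to 4) cannot produce a total below 3, so as written the favourable category of primary outcome 1 is empty

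*Protocol article*

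**What the plan says.** **AUDIT-C.** The Substance abuse section of the protocol article calls the instrument a "three-item questionnaire of problematic alcohol use" and describes its items: "The three questions, each with a range of 1 to 4, cover the frequency of" drinking days, usual number of drinks, and days of heavier drinking. It reports good performance "at a cut point of 3 or greater for identifying risky drinking (0) or not (1"). The Fifteen outcomes section lists as the first primary outcome "Alcohol Use Disorders Identification Test (AUDIT-C) score < 3 (i.e., problematic alcohol use").

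**CES-D.** The Mental health section states "Mental health is evaluated by 20 items, each with a response range from 0 to 3" and then: "Participants with a CES-D score greater than 16 are considered to have a depressed mood (0) and those < 16 are not (1"). The Fifteen outcomes section lists the last primary outcome as "Center for Epidemiologic Studies of Depression (CES-D) score < 16 (i.e., caseness"). It adds: "Each primary outcome measure is a binary variable (not present or present").

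**Use in the primary analysis.** Under Outcome measures, each of the 15 outcomes is tested at 0.05 two-sided, the significant ones are counted to give the NSO, and at least three are required to declare the treatment effective.

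**The concern.** The favourable category of outcome 1 is a total below 3. With the item range that the article gives, an abstainer who takes the lowest option on every question already scores 3 and is classed as a risky drinker. An outcome on which every participant has the same value cannot separate the conditions.

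What is at stake is one of the 15 components of the primary endpoint, in a trial whose coaches are trained to reduce alcohol and drug use and to practise brief alcohol interventions (Condition 2: soccer league).

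This is not a detail that a condensed article may leave to a fuller document. The scoring is stated, and its two parts disagree.

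**Working it through.** **Inputs, all from the protocol article**
- AUDIT-C: 3 items, each 1 to 4; 3 or more coded 0, otherwise 1 (Substance abuse). Favourable outcome: score below 3 (Fifteen outcomes).
- CES-D: 20 items, each 0 to 3; above 16 coded 0, below 16 coded 1 (Mental health). Favourable outcome: below 16 (Fifteen outcomes).
- NSO: 0.05 per outcome, threshold of three out of 15 (Outcome measures).

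**Assumption.** The AUDIT-C score is the plain sum of its three items. The article does not say so, but it gives no other rule and no zero or skip code for non-drinkers.

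**Step 1: AUDIT-C as stated**
- Lowest total = 3 × 1 = 3; highest = 3 × 4 = 12.
- There are 4 × 4 × 4 = 64 possible answer patterns, and 0 of them total less than 3. All 64 are coded 0.

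**Step 2: the same cut on an item scale starting at 0**
- With items from 0 to 4 (an assumption, for comparison only), totals run from 0 to 12. There are 5 × 5 × 5 = 125 patterns. Those totalling 0, 1 or 2 number 1 + 3 + 6 = 10.
- So a cut at 3 divides a scale that starts at 0 and cannot divide one that starts at 3.

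**Step 3: effect on the NSO**
- If outcome 1 is constant, at most 15 − 1 = 14 outcomes can contribute.
- With independent outcomes and no treatment effect, the chance of at least three significant results is 1 − Σ C(n, k) × 0.05^k × 0.95^(n−k), summed over k = 0, 1, 2.
- n = 15: 0.0362.
- n = 14: 0.0301.
- The direction does not depend on independence. With the threshold fixed at three, removing an outcome from the count can never raise the count.

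**Step 4: CES-D**
- Totals run from 0 to 20 × 3 = 60, which is 61 integer values.
- Under the Mental health wording, exactly one of them, 16, receives no code. Under the Fifteen outcomes wording (below 16 or not), 16 is coded 0.

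**Step 5: labels**
- The Fifteen outcomes section attaches the terms for problem drinking and for caseness to the low scores. The Substance abuse and Mental health sections attach those meanings to the high scores. The numerical definitions and 0/1 codes agree across sections; only the glosses are on the wrong side.

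**The case against.** The best defence is that the error is a single descriptive phrase. The Substance abuse section credits the cut of 3 with good specificity. A cut that flags everyone has no specificity, so the authors must have in mind a scale with totals below 3. The outcome definition itself is the same in both sections. This stands: the item range is the likelier culprit, and the stored data may be sound. It does not remove the contradiction, because the article does not show which coding the phone form uses.

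A reader might infer several stronger things that the document does not support:

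- **That every man has in fact been coded 0.** This follows only if the items are stored from 1, summed, and cut at 3. The article shows the rule, not the data.
- **That the outcome 1 model cannot be fitted.** The Data analysis section plans Bayesian mixed models. Such a model may run on a constant outcome and return output driven by its priors. The sound statement is that the data would carry no information on condition. For the same reason, a software failure should not be relied on to expose the error.
- **That a threshold set for 15 outcomes gives the wrong error rate with 14.** The false-positive chance falls (Step 3), so the test becomes more conservative.
- **That alcohol drops out of the primary endpoint.** The 24-hour alcohol outcome and the PEth test remain, and the continuous AUDIT score is analysed secondarily (Missing data section).
- **That the reversed labels bias the result.** The plan counts two-sided significance, and swapping the names of two categories leaves a two-sided p value unchanged.
- **That a CES-D of 16 is undefined throughout.** The list of primary outcomes largely settles it as not favourable.

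It is also tempting to say that the cut should simply move up by 3 if the items run from 1. Items of 1 to 4, moved to start at 0, run from 0 to 3 and total 0 to 9. The article does not show that the cut of 3 belongs to that scale rather than, say, one totalling 0 to 12.

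**Conclusion.** The point holds in a conditional form. As written, the AUDIT-C item range and the cut point are incompatible. If the score is a plain sum and is coded as stated, 100% of men are coded 0 on primary outcome 1, and at most 14 of 15 outcomes can reach the NSO. The cost is a lost chance to detect benefit. Its effect on power cannot be sized, because the article gives no expected AUDIT-C effect. Type I error is not inflated, and the sample size calculation, which uses employment and hard drug use, is not affected.

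This is a wrong scoring rule in a primary outcome and is cheap to correct, so it should be corrected. The CES-D gap (one value of 61) and the misplaced labels are minor wording faults.

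**What to change.** 1. Check the item coding stored in the mobile-phone form, including how non-drinkers are recorded.
2. State the item range and the summing rule, and reconcile them with the cut point before outcome 1 is derived. Two conditions should be met: an abstainer falls in the favourable category, and the cut is applied on the scale for which it was established.
3. Tabulate the AUDIT-C total once, without regard to condition, to confirm that both categories occur.
4. In the Mental health section, code CES-D of 16 or more as 0 and below 16 as 1, to match the list of primary outcomes.
5. In the Fifteen outcomes section, move the two labels to the unfavourable categories.

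The cost is a few words of text and one check of the data-entry coding. No change to the design, sample size or NSO threshold is needed. Recruitment was still under way when the article was submitted.

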#### Recent HIV testing

Recent HIV testing is self-reported as occurring (1) in the last 3 months or not (0).

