## Background

The DREAMS Initiative was launched by global donors to reduce adolescent and young women’s risks for acquiring HIV [1]. Concurrently, Option B+ is being broadly implemented to eliminate perinatal HIV transmission and increase the length and quality of the lives of women living with HIV in sub-Saharan Africa [2]. While women almost always acquire HIV from their male partners, there are few such initiatives for men nor have men been successfully engaged in HIV prevention or care [3]. This study examines a gender-specific HIV prevention strategy for South African men.

HIV incidence among young, black men in South Africa has remained stable at 3% per year [4], resulting in 2.4 million South African men infected with HIV [5, 6]. New infections occur at an older age among men compared with women [6] and are associated with a cluster of risky behaviors. For example, poly substance use is endemic in South Africa; about 30% of young men report visiting bars more than 10 times per month, 30% have symptoms of alcohol dependency, 50% have recently used marijuana, 32% use methamphetamine, and 20% use mandrax (methaqualone/quaalude, a sedative/hypnotic) [7–11]. Substance use often leads to township violence [12] and is linked to 60% of automobile accidents, 75% of homicides, 67% of domestic violence, and 30% of hospital admissions [13]. Alcohol use alone costs South Africa about 9 billion South African Rand (ZAR) annually [14]. Furthermore, about half of township men have been arrested or are in jail, 22% have been in prison, and 20% report being gang members [11]. More than a third of young men have had recent concurrent sexual partnerships, fail to use condoms [15–18], and experience repeated sexually transmitted infections (STIs) [19, 20]. Almost 30% of young men report that at some point they have forced a woman to have sex [11]. Thus, there are substantial data showing that South African men are in need of efficacious interventions to reduce their risk for HIV, and their HIV risk appears related to a cluster of risky acts.

While men experience many risks, HIV prevention resources are primarily anchored in healthcare settings—a setting underutilized by men [21, 22]. In particular, most women find out about their HIV infection in antenatal care, a setting which men are typically excluded from visiting [22]. Seropositive men seek care at much later stages of disease than women [23].

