### Recruitment

Recruiters underwent 1 month of training. Recruiters go dwelling-to-dwelling, randomly selecting the first household (by flipping a coin on a hardcopy neighborhood map, with a supervisor) to enter and then systematically approach houses in concentric circles until 50 young men aged 18–29 are identified per neighborhood and agree to participate, documenting all refusals. To be considered eligible, young men must be aged 18–29, have slept at least four nights per week in the household for the 2 months prior to recruitment, speak Xhosa or English, do not appear to be under the influence of any substances at the time of recruitment, and are able to understand the recruiter. Any potential participant who does not meet the five inclusion criteria defined above is considered ineligible and is not invited to participate in the study. We anticipate that it may take several household visits to contact and recruit the young men identified by their family members on recruitment visits. Since housing units are typically too small to provide confidential interviewing, we transport young men to a local storefront research study space to complete assessments. Recruiters remain in constant contact with drivers, so that when a potential participant expresses interest, the driver can both confirm that they live within the catchment area and transport them to the local storefront assessment center.

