#### Concurrent sexual partnerships and condom usage

Concurrent sexual partnerships are self-reported as having sexual partnerships overlapping in occurrence in the last 3 months (0) or not (1). Condom usage is always using condoms in the past 3 months (1) or not (0). No sex counts as (1).

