### Secondary outcomes

#### HIV prevention and treatment continua

Among seronegative participants, self-reports document the utilization of repeat HIV testing, access of medical care, discussions of HIV prevention with sexual partners, and disclosure of serostatus. Among participants living with HIV, participants self-report engagement in medical care, uptake and adherence to antiretroviral (ARV) medications, and medical regimens over time. HIV testing is offered at the soccer fields by a mobile testing van and uptake is documented. Given the low self-reported rate of HIV positivity, we ask if participants want to share results as they test in real time at the 6-, 12-, and 24-month assessment. The key comorbidities affecting the HIV continua are included in the fifteen study outcomes (e.g., mental health symptoms, substance abuse, violence toward women).

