#### Process measures for soccer

Using a mobile phone survey programmed by Mobenzi at each practice or game, coaches report on: attendance, whether HIV, alcohol and drug RDT are administered, the content area discussed during the coaching meeting (e.g., alcohol use, sexual relationships), and the skills used by the coach. Stellenbosch supervisors randomly visit either practices or games once every 2 weeks to provide on-site supervision and monitoring. HIV testing is offered at the soccer field by a mobile testing van and uptake is documented (but not the test results). RDT for alcohol, marijuana, methamphetamine, and mandrax are administered randomly once per week to all participants.

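### The recent-HIV-testing outcome scores men who already know they are HIV-positive, and have not retested, as failures; the effect is a mild dilution and possibly a modest bias against an arm that diagnoses more men

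*Protocol article*

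**What the plan says.** - The section on fifteen outcomes lists "7) HIV testing in the last 3 months" as a primary outcome and adds: "Each primary outcome measure is a binary variable (not present or present". There is no not-applicable value.
- The section on recent HIV testing gives the coding: "Recent HIV testing is self-reported as occurring (1) in the last 3 months or not (0".
- The Recruitment section sets the entry rule: "Any potential participant who does not meet the five inclusion criteria defined above is considered ineligible". The five criteria are age, residence, language, no apparent intoxication and ability to understand the recruiter. HIV status is not among them, so men living with HIV are enrolled.
- The secondary outcomes (HIV prevention and treatment continua) record repeat testing for seronegative men. For the others the measure is care and antiretroviral use: "Among participants living with HIV, participants self-report engagement in medical care". The same section describes self-reported positivity as low, without a figure.
- For condom use the article does settle the comparable case, where the behaviour does not arise: "No sex counts as (1".
- The active arms have an extra route to testing: "HIV testing is offered at the soccer field by a mobile testing van and uptake is documented". The same sentence says that the test results are not recorded. Control men receive flyers and are contacted only for assessments.
- The Data management section provides HIV rapid tests at each scheduled assessment, without limiting them to any arm.

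**The concern.** A man who knows he is HIV-positive has no evident reason to seek another test. The coding gives him the unfavourable value unless he retested or was diagnosed within the last 3 months. Two consequences follow.

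**Dilution.** Men whose score cannot respond to the intervention pull the observed rate down in every arm and shrink the difference between arms in proportion.

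**Direction.** Coaches are trained to increase HIV testing, and the van tests at the fields. Soccer in the SL arm lasts 1 year, and the main time point is 24 months. A man diagnosed through the intervention in the first year will usually be outside the 3-month window at 24 months and score 0. If the active arms diagnose more men than control, the coding counts part of that success against them. The planned contrast is change from baseline, which does not remove status learned after baseline.

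At stake is one of 15 outcomes, under a rule that requires at least three significant ones.

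**Working it through.** **Inputs from the article (sample-size text):** 400 men per condition, 20% loss, design effect 1.49 × 1.16 = 1.7284, alpha 0.05 (two-sided, from the outcome section), power 80%, reference rate 30%.

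**The plan's own figure.** For 30% v 17%, the two-proportion formula with continuity correction gives 181 men per arm. Then 181 × 1.7284 / 0.8 = 391.05, rounded up to 392, close to the planned 400. (Without the correction: 359.) The sample size therefore reproduces for this pair. The article gives no figure for HIV testing.

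**Effective size.** 400 × 0.8 / 1.7284 = 185 men per arm.

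**Assumptions not in the article:**
- Among men not known positive, the testing rate is 30% in control and 44% in an active arm. This 14-point difference has 79.9% power at 185 per arm.
- Known-positive men do not retest.
- The known-positive share q is 3% to 10%. The article gives only the description of self-reported positivity as low, and the background statement "HIV incidence among young, black men in South Africa has remained stable at 3% per year".

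**Formulas.** Observed rate in an arm = (1 − q) × p. Power = Φ{[d − 1.96 √(2p̄(1 − p̄)/n)] / √[(p₁(1 − p₁) + p₂(1 − p₂))/n]}.

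Example, q = 3% in both arms: control 0.97 × 0.30 = 0.291; active 0.97 × 0.44 = 0.4268; d = 0.1358. Power = Φ[(0.1358 − 0.0977)/0.0494] = Φ(0.77) = 78.0%.

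**Equal share in both arms.** The fair comparator is not 79.9%, because excluding known positives also loses men. It is 30% v 44% with 185 × (1 − q) men per arm.

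| q | Difference as written | Power as written | Power if excluded | Cost of the rule |
|---|---|---|---|---|
| 3% | 13.6 points | 78.0% | 78.7% | 0.7 |
| 6% | 13.2 points | 76.0% | 77.4% | 1.5 |
| 10% | 12.6 points | 73.2% | 75.6% | 2.5 |

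**More known positives in the active arm (control 3%).**

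| Active arm | Difference as written | Power as written | Shift if testing is 30% in both arms |
|---|---|---|---|
| 4% | 13.1 points | 75% | −0.3 points |
| 5% | 12.7 points | 73% | −0.6 points |
| 6% | 12.3 points | 70% | −0.9 points |

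The last column is 0.30 × (0.03 − q in the active arm). Of the fall from 80% power, 2 points come from the common 3% and the rest from the extra diagnoses.

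**Scoring every known-positive man 1.** Observed rate = (1 − q) × p + q. At equal shares of 3%, 6% and 10%, power is about 76.6%, 73.3% and 68.8%, lower than the present rule each time. With no true effect on testing and shares of 3% v 6%, it creates 0.70 × 0.03 = +2.1 points in favour of the active arm, against −0.9 under the present rule.

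**The case against.** **The article is condensed, and the denominator may be set elsewhere.** The testing section is one sentence and does not say outright that known-positive men count as failures. That is fair as to wording. But the rule is stated for all men, no not-applicable value exists, and the same article settles the comparable condom case. As published, the coding gives these men 0.

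**Control men can be diagnosed too.** Rapid tests at assessments are available in all arms, and every arm has 6- and 12-month visits before the 24-month endpoint. This stands. It narrows the gap in diagnoses, though it does not remove the extra route at the soccer fields.

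**The power model is not the planned test.** The plan uses a change-from-baseline contrast with two degrees of freedom and a random effect for each man. Men who score 0 at both baseline and 24 months may be partly absorbed by that model. This also stands: the figures show direction and rough size only.

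**A stronger reading is tempting.** A reader might infer a serious loss, for example 6% known positive in control v 10% in an active arm, which gives an 11.4-point difference and 64% power. The article gives no basis for shares that high or that far apart, and it calls self-reported positivity low. A reader might also set the equal-share results against 80% and see a loss of 2 to 7 points; most of that loss remains when known positives are excluded.

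**Conclusion.** The point holds in a limited form. As written, the coding misclassifies men who know they are HIV-positive and have not retested, and it departs from the article's own handling of repeat testing in the secondary outcomes. The cost is about 1 to 2.5 power points if 3% to 10% of men in every arm are known positive. With 1 to 3 points more diagnosed men in an active arm (3% v 4% to 6%), the cost is larger but still modest.

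The known-positive shares, the testing rates, the absence of retesting and the extra diagnoses are all assumed. The documents do not support a claim that the comparison is materially biased against the intervention, or that the NSO verdict would change. With one item of 15 and a threshold of three, the effect on the verdict is probably small, and no NSO calculation was made.

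**What to change.** - **Primary definition:** state that the HIV-testing outcome is assessed among men who do not self-report being HIV-positive at baseline. Status at baseline cannot be affected by the intervention, so this restriction does not disturb the comparison.
- **Sensitivity analysis 1:** keep the current coding in all men.
- **Sensitivity analysis 2:** count men who self-report a diagnosis after baseline as having met the outcome. The primary definition still scores most of these men 0, so this analysis addresses the possible bias against an arm that diagnoses more. It relies on voluntary disclosure, because van results are not recorded and sharing results at assessments is optional. Disclosure may differ by arm, and crediting diagnoses leans towards the arm with more of them, so it should not be primary.
- **Do not** score all known-positive men 1.

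The cost is a sentence of definition and a slightly smaller denominator for this one outcome: at 3% to 10% known positive, about 180 to 167 effective men per arm instead of 185. The article implies that HIV status is self-reported but does not say so for the baseline visit; that should be confirmed. Recruitment was still under way at submission, so the rule could be set before outcome analysis.
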